### Quality Control and Quality Assurance

Two neuroscientists, a neuroimaging specialist and an expert in geriatrics, worked together to examine the participants and provide a diagnosis for each participant. In addition, training was provided for all researchers, while all items involved in the test, such as blood samples, EEG data processing and neuropsychological assessments were monitored by the quality control committee who randomly selected data samples to send to a third party for retesting or re-evaluation. Data entry was performed by EpiData Entry software and was also monitored by the quality control committee who further randomly selected the input information and paper information. To control the impacts of clinical treatment, we strictly restricted medication. Oral medication before and during hospitalization as well as during follow-up remained unchanged except for sudden diseases, such as cardiovascular and cerebrovascular accidents and aggravation of primary diseases. If there are errors, the sampling proportion will be expanded, while if the input error proportion is high, a second person needs to check and correct the input data. Moreover, all data were monitored and reviewed by the principal investigator or research coordinators.

### Biomarker Test of Blood Samples

Aβ1-42, Aβ1-40, p-tau217 and other indicators of the plasma were detected by liquid phase flow cytometry (using the MSD platform) before and after treatment to evaluate the outcome of pathological indicators. Specifically, blood samples were collected at 7:00 a.m. before and after treatment, and plasma samples were obtained after centrifugation for MSD detection.

### Statistical Methods

#### Statistical Analysis Methods

(1) Descriptive analysis: the counting data was presented as the mean ± standard error; (2) the counting data was compared between groups by performing the continuous correction χ^2^-test, when the theoretical frequency of more than 25% cells was less than 5. The Fisher exact probability method was adopted; the independent sample *t*-test was conducted for comparison between groups of normally distributed measures; repeated-measures ANOVA was employed to analyze repeated data between groups in different time. For non-normally distributed measures, the Wilcoxon rank sum (WRS) test was used for comparisons between groups.

#### Statistical Hypothesis

The primary endpoint of this study was the end of treatment and completion of the 3-month follow-up for all subjects, and its indicator was the MMSE score. Apart from that, the study hypothesis is to demonstrate the superiority of HF-rTMS over LF-rTMS in transcranial magnetic stimulation protocols for patients with Alzheimer’s disease. In terms of subgroup analysis, the HF treatment group was preferentially compared with the low-frequency treatment group of non-APOE4 carriers; if the statistical result of *P*-value is less than 0.05, then the comparison between the HF treatment group and the low-frequency treatment group of APOE4 carriers is made in order. If the statistical result of *P*-value is less than 0.0125, then the comparison among the four subgroups is considered significant.

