### Outcomes

The primary end point is the quantitative index, namely MMSE, whereas the secondary outcome measures are MoCA, ADAS-cog, GAD-7, CES-D, and ADL.

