### Sample Size Calculation

The sample size of this project was calculated by Pass software on the basis of previous literature. In this study, the MMSE scores of the HF-rTMS group and the LF-rTMS group were 10.4 ± 1.7 and 10.2 ± 1.8, respectively, before treatment. After 2 weeks of rTMS treatment, their MMSE scores reached 11.2 ± 1.9 and 8.8 ± 2.3, respectively (Ahmed et al., 2012), when the target effect size had 80% power (β = 0.10) and a type I error was 5% (α = 0.05). In addition, the group sample size of 13 and 12 achieved 81% power for detecting a difference of 2.4 between the null hypothesis and that the mean of both groups is 11.2 and the alternative hypothesis that the mean of Group 2 is 8.8 with known group standard deviations of 1.9 and 2.3 and a significance level (alpha) of 0.050 using a two-sided two-sample *t*-test, while the sample size of each subgroup is at least 13. Considering the loss of follow-up, falling off and sample data being eliminated due to data quality, the sample size should be increased by 20%. Thus, the final sample size of each subgroup are at least 16. Furthermore, the ratio of APOE4 carriers to non-APOE4 carriers are set to 3:2 according to the comparison of population samples and our previous study. Other than that, in this study, 80 participants, with 48 APOE4 carriers and 32 non-APOE4 carriers will be recruited.

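### The primary MMSE endpoint is tied to both end of treatment and 3-month follow-up with no rule for which governs, while the sample size supports only a single 2-week test

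*Protocol article*

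**What the plan says.** Four sections of the protocol article bear on when the primary endpoint is measured.

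- **Outcomes:** "The primary end point is the quantitative index, namely MMSE". No time is attached.
- **Statistical Hypothesis:** "The primary endpoint of this study was the end of treatment and completion of the 3-month follow-up for all subjects", with the MMSE score as its indicator. The section then sets a fixed order for the high- versus low-frequency comparison (non-carriers first, carriers only if the first P-value is below 0.05) and a threshold of 0.0125 for comparisons among the four subgroups. Neither rule mentions time points.
- **Sample Size Calculation:** "After 2 weeks of rTMS treatment, their MMSE scores reached 11.2 ± 1.9 and 8.8 ± 2.3, respectively", and on that basis "the group sample size of 13 and 12 achieved 81% power for detecting a difference of 2.4", at "a significance level (alpha) of 0.050 using a two-sided two-sample" t-test. No 3-month difference, SD or between-time correlation is given.
- **Randomization and Allocation:** the allocation is withheld until the primary endpoint has been met at follow-up for all participants.

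Statistical Analysis Methods lists a repeated-measures ANOVA for data collected at different times, but does not name it as the primary test.

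**The concern.** The article does fix the endpoint time, but in a way that allows at least three readings: success at either time, success at both, or success at 3 months alone. Each has a different type I error or power, and only a 2-week test matches the sample size.

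MMSE is assessed weekly during treatment and monthly over six months of follow-up, so several scores will be available to choose from. Unless the governing time is settled before the arms are revealed, a reader cannot rule out that it was chosen after the results were known. Nor can a reader tell what a significant result at one time and a null result at the other would mean for the main claim.

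**Working it through.** **Inputs from Sample Size Calculation.** Means 11.2 and 8.8 (difference 2.4), SDs 1.9 and 2.3, n = 13 and 12, two-sided alpha 0.05. **From Randomization and Allocation:** 16 per arm in non-carriers, 24 in carriers, 40 overall. **Assumed, because the article does not give it:** the correlation ρ between the 2-week and 3-month test statistics, taken as 0.5 to 0.9.

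**Step 1: reproduce the stated power.** The calculation is described "with known group standard deviations of 1.9 and 2.3", which points to a normal test.

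SE = √(1.9²/13 + 2.3²/12) = 0.848; 2.4/0.848 = 2.831; power = Φ(2.831 − 1.960) = 80.8%.

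This matches the stated 81%, which therefore belongs to one test at 2 weeks.

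**Step 2: either time suffices, each tested at 0.05.** Under the null, type I error = 1 − P(|Z₁| < 1.96 and |Z₂| < 1.96) for a bivariate normal pair with correlation ρ.

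| ρ | Type I error per comparison |
|---|---|
| 0.5 | 9.1% |
| 0.7 | 8.4% (8.35%) |
| 0.9 | 7.0% |

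Independence would give 1 − 0.95² = 9.75%. None of these depends on sample size.

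**Step 3: both times required, with the full 2.4-point difference and the same SDs at 3 months.** Power = P(Z₁ > 1.96 and Z₂ > 1.96), each Z having mean 2.4/√(1.9²/n₁ + 2.3²/n₂). The sizes after loss are 80% of the recruited numbers: 16 × 0.8 = 12.8 (about 13, the plan's own evaluable target), 24 × 0.8 = 19.2 (about 19), 40 × 0.8 = 32.

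| Comparison | n per arm | Power, ρ 0.5 to 0.9 |
|---|---|---|
| Plan's own calculation | 13/12 | 70% to 76% |
| Non-carriers after 20% loss | 13/13 | 72% to 78% |
| Non-carriers, no loss | 16/16 | 83% to 86% |
| Carriers after 20% loss | 19/19 | 89% to 92% |
| Carriers, no loss | 24/24 | 96% to 97% |
| Overall after 20% loss | 32/32 | 99% |
| Overall, no loss | 40/40 | above 99% |

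Only non-carriers at the planned evaluable size fall below 81%.

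**Step 4: only 3 months counts.** There is no 3-month difference or SD to enter. As an illustration with the 2-week SDs and a Welch t-test at 13 per arm, power is 79% for a difference of 2.4, 55% for 1.8 and 29% for 1.2. The article does not say which of these, if any, applies.

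**The case against.** The strongest reply is that the sentence describes a milestone rather than two co-primary times. Completion of follow-up for all subjects is the language of a data cut, and Randomization and Allocation uses the word endpoint in that way when it ties unblinding to follow-up. On that reading 3-month MMSE may be the single primary time, and the figures in Steps 2 and 3 would not apply. This stands as a possible reading, and it is why two co-primary times should not be taken as established. It does not remove the problem: the power then rests on a 2-week effect applied to a 3-month score.

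A second reply is that one repeated-measures ANOVA test of the arm difference across both times would hold alpha at 5%. That is true of such a test, but it is listed generically, and the sample size is for a two-sample t-test.

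A reader might infer that the plan has no multiplicity control and uses 0.05 throughout. The documents do not support that: there is an ordered subgroup test and a 0.0125 threshold. What is absent is any rule for time.

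A reader might also infer that requiring both times would leave the whole trial underpowered. Step 3 does not support that: under the plan's own difference and SDs, the carrier and overall comparisons stay well above 81%, as do non-carriers if nobody is lost. Nor does the article say that the effect fades by 3 months; it is silent.

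Finally, the full protocol or an analysis plan may settle the matter. That is possible, but the article itself states the endpoint time, and states it ambiguously and out of step with its own sample size.

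**Conclusion.** The concern holds in a limited form. The primary time point is ambiguous, and no reading that gives the 3-month score a primary role leaves both the 5% alpha and the 81% power supported as written.

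- **Either time:** error of about 7.0% to 9.1% per comparison, resting on the assumed correlation of 0.9 to 0.5.
- **Both times:** power of about 70% to 78% for non-carriers at 12 to 13 per arm, and above 81% elsewhere, resting on that correlation and on the full 2.4-point difference and the 2-week SDs still holding at 3 months. The non-carrier shortfall matters beyond its size, because that comparison comes first in the order and failing it stops the carrier test.
- **3 months alone:** the power is unsupported, and no figure can be given from the article.

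Which consequence applies cannot be decided from the text. That the text must be settled before unblinding by arm does not depend on the answer.

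**What to change.** Before allocation is revealed, name one primary MMSE time point and use the same wording in Outcomes and Statistical Hypothesis.

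- **If 2 weeks:** the existing sample size applies. Make 3-month MMSE a secondary endpoint tested at 0.05 only after the 2-week test succeeds, and state where that test sits relative to the non-carrier-then-carrier sequence, so that the alpha path across time and subgroup is complete. Record that 2-week scores of 18 patients have already been analysed by genotype but not by arm (Results in Progress), so that the basis for the choice is visible.
- **If 3 months**, as the unblinding rule may suggest: restate the power in Sample Size Calculation under an explicit 3-month difference and SD, and make the 2-week score the secondary.

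In either case, name the test used for the primary comparison. The first option costs a few sentences and no added patients; the second needs a new calculation, which may or may not change the sample size. In both, the other time point becomes a conditional secondary claim, a small loss.

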We believe that different APOE4 carriers should be given different treatment schemes than non-APOE4 carriers because of the excitability of their neural networks is different. The APOE4 carriers have increased network excitability due to the impairment of GABAergic interneuron function (Najm et al., 2019). Compared with the APOE ε3 allele, APOE ε4 allele increases Ca^2+^ excitability due to lysosome dysregulation and impaired modulation of Ca^2+^ responses upon changes in extracellular lipids (Larramona-Arcas et al., 2020). Traditional theory suggests that high-frequency rTMS increases cortical excitability by inducing long-duration enhancement potentials, while low-frequency rTMS decreases cortical excitability by inducing long-duration inhibition potentials (Pell et al., 2011). GABAergic neuronal receptor activity is mainly associated with chloride channel opening (Traub et al., 2003), and high-frequency stimulation is more likely to induce long-term potentiation (LTP) (Pell et al., 2011). Hence, high-frequency treatment contributes to more gamma oscillatory activity and better therapeutic effects. However, for APOE4 carriers with more significant loss of GABAergic neurons (Knoferle et al., 2014; Najm et al., 2019), HF treatment may be less effective. In this case, low-frequency therapy may be more suitable for that kind of patients. Therefore, in this study, it is believed that different transcranial magnetic stimulation regimens should be selected for AD patients based on APOE genotypes, so as to obtain precise treatment strategies.

In summary, this paper aims to study the difference in the efficacy of different rTMS strategies in AD patients with different APOE genotypes, and analyze the changes of gamma oscillations.

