## Objectives

The primary objective of the study is to analyze the different efficacies of rTMS in AD patients with different APOE genotypes, so as to provide the basis for the precise treatment of AD.

The secondary objective is to analyze the changes in gamma oscillations and pathological indicators in different APOE genotypes, thus being conducive to the precise treatment of AD.

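### The stated hypothesis and test order do not address the primary objective: no stated test compares the HF-LF difference between APOE4 carriers and non-carriers

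*Protocol article*

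**What the plan says.** The Objectives section states: "The primary objective of the study is to analyze the different efficacies of rTMS in AD patients with different APOE genotypes". The Introduction closes in the same terms: "this paper aims to study the difference in the efficacy of different rTMS strategies in AD patients with different APOE genotypes". It also gives an expected direction. HF may work less well in APOE4 carriers, because of their loss of GABAergic neurons, and "low-frequency therapy may be more suitable for that kind of patients".

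The Statistical Hypothesis section fixes something else: "the study hypothesis is to demonstrate the superiority of HF-rTMS over LF-rTMS in transcranial magnetic stimulation protocols for patients with" Alzheimer's disease, with no reference to genotype. Genotype enters only as a subgroup analysis, in three steps:

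- First, "the HF treatment group was preferentially compared with the low-frequency treatment group of non-APOE4 carriers".
- If that gives P < 0.05, "then the comparison between the HF treatment group and the low-frequency treatment group of APOE4 carriers is made in order".
- Last comes a comparison of the four genotype-by-frequency cells, judged at P < 0.0125. The contrast is not given.

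The Statistical Analysis Methods section lists chi-square or Fisher tests, t-tests, Wilcoxon tests and repeated-measures ANOVA over time. It names no genotype-by-frequency term. The Sample Size Calculation rests on a single two-group HF-LF comparison applied to each subgroup.

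**The concern.** The objective is a question of effect modification: is the HF-LF difference in MMSE the same in carriers and non-carriers? The stated hypothesis is an average effect over all patients. For carriers, who are 48 of 80 (60%), it points away from the direction that the Introduction suggests.

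Two separate stratum tests do not fill the gap. A significant result in one stratum and a non-significant one in the other is not evidence that the effects differ, and here the strata also differ in size (24 against 16 per arm). The gate adds a second problem: if non-carriers miss P < 0.05, carriers are not formally compared at all. The four-subgroup step does not help as written, because an omnibus or pairwise comparison of four cells mixes the main effects of frequency and genotype with their interaction.

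At stake is the trial's central conclusion. Genotype-guided rTMS could be supported, or dismissed, on results that never estimate the relevant contrast.

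**Working it through.** **Inputs.** SDs 1.9 (HF) and 2.3 (LF), difference 2.4, two-sided alpha 0.05, 20% allowance for loss (Sample Size Calculation). Allocation 24/24 carriers and 16/16 non-carriers (Randomization and Allocation). Pooled SD = √((1.9² + 2.3²)/2) = 2.11. After 20% loss, about 19/19 and 13/13.

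**The plan's own figure.** With 13 and 12 patients and known SDs, power = Φ(2.4/√(1.9²/13 + 2.3²/12) − 1.96) = 80.8%. The stated 81% reproduces. It is the power of one HF-LF comparison within a subgroup, not of a comparison between genotypes.

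**Overall HF-LF test, 40 per arm.** Average effect = 0.4 × (non-carrier effect) + 0.6 × (carrier effect). SE = 2.11 × √(2/40) = 0.472.
- +2.4 in non-carriers, 0 in carriers: 0.4 × 2.4 = 0.96; power 52%.
- +2.4 and −2.4 (assumed): 0.96 − 1.44 = −0.48; chance of showing HF superior 0.2%.

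**Gated stratum tests when both genotypes truly respond alike** (two-sample t-test power). The plan gives 2.4 as its HF-LF effect. The second value, 1.65, is an assumption; in the Introduction it appears only as an HF-versus-sham result.

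| Common effect | Per arm (carriers / non-carriers) | Power, non-carriers | Power, carriers | Non-carriers significant, carriers not | Carriers untested |
|---|---|---|---|---|---|
| 2.4 | 24 / 16 | 0.875 | 0.971 | 2.5% | 12% |
| 2.4 | 19 / 13 | 0.794 | 0.926 | 6% | 21% |
| 1.65 | 24 / 16 | 0.572 | 0.756 | 14% | 43% |
| 1.65 | 19 / 13 | 0.482 | 0.650 | 17% | 52% |

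The fifth column is (power in non-carriers) × (1 − power in carriers), for example 0.572 × 0.244 = 0.14. The last is 1 − (power in non-carriers).

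**Interaction test.** SE = 2.11 × √(2/24 + 2/16) = 0.963; after loss, 2.11 × √(2/19 + 2/13) = 1.074. Noncentral t:
- 2.4-point difference in effects: 69% (59% after loss).
- 4.8 points (the ±2.4 crossover): over 99% at full numbers.

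**Sensitivity to the SD.** Table 2 runs means and SDs together in the copy read, but its MMSE SDs appear to be about 6 to 9. At 6.2 and 8.7 without baseline adjustment, the interaction SE is 2.83 and 3.97. Power is then about 13% and 9% for 2.4 points, and about 39% and 22% for the crossover.

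**The case against.** The strongest reply is that this is a condensed article. A statistical analysis plan may exist, and the repeated-measures ANOVA could carry a genotype term. That limits the claim: a reader might infer that the interaction will never be tested, and the document does not show that. What it does show is a stated hypothesis and test order that do not match the stated objective. An analysis plan that made the interaction primary would depart from them.

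Two other stronger readings also fail:

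- A reader might infer that the overall test must fail if the trial's theory is right. The Introduction is hedged: HF may be less effective and LF may be more suitable in carriers. Exact cancellation needs an LF advantage of 1.6 points in carriers (0.4 × 2.4 = 0.6 × 1.6), a value found nowhere in the document. If carriers have no HF-LF difference, power is reduced to 52%, not lost.
- A reader might infer that the two stratum tests would disagree in about half of trials under equal effects. At 1.65 points the chance that exactly one is significant is 46% (51% after loss), but only if both are always run. The gate rules out the pair in which carriers alone are significant. The planned sequence gives the misleading pair in 14% (17%), and in 2.5% (6%) at the plan's 2.4 points. The larger cost of the gate is that carriers go untested.

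It is also fair to say that the interaction test is weak at 80 patients. That stands and must be disclosed, but it does not make a different test an answer to the question.

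**Conclusion.** The concern holds in this form: the hypothesis and test order fixed in the Statistical Hypothesis section do not address the primary objective, and no stated test or interval compares the HF-LF difference between genotypes. The four-subgroup comparison does not repair this, because its contrast is undefined.

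How much this matters depends on the true effects. The overall test ranges from 52% power to a 0.2% chance of showing HF superior under the two patterns of genotype difference examined. Under equal effects, the risk of a spurious contrast is small at 2.4 points and moderate at 1.65, while the risk that carriers are left untested runs from 12% to 52%. These figures assume the plan's SDs, independent strata and, for the overall test, an SD of 2.11 in each arm. The 1.65 common effect and the −2.4 carrier effect are assumptions.

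**What to change.** In the Statistical Hypothesis section:

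- Make the frequency-by-APOE4 interaction on MMSE the test of the primary objective, two-sided 0.05, in one model of all 80 patients with baseline MMSE as covariate. Name one of the plan's stated time points (end of treatment or 3 months) as primary.
- Report the HF-LF difference with 95% CI in both strata whatever the P-values, and drop the gate.
- Make overall HF against LF a secondary estimate.
- State that no genotype-specific conclusion will rest on one stratum being significant and the other not.

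The cost is one model term and revised wording. Randomisation is already stratified by genotype, no new data are needed, and the article reports that allocation has not been unblinded.

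The downside to state openly is power: 69% for a 2.4-point interaction at SD 2.11 (59% after loss) and over 99% for the ±2.4 crossover, but only about 9-13% and 22-39% if the SDs are 6.2 to 8.7 without baseline adjustment. Adjustment would raise these by an amount the document does not give. At the plan's SDs, 80% power for 2.4 points needs about 101 evaluable patients at the 3:2 ratio (normal approximation: (1.96 + 0.84)² × (1.9² + 2.3²) × (1/0.3 + 1/0.2)/2.4²), against 80 recruited.

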### Results in Progress

Our study is still in progress. Our current data are the preliminary data of the RCT study, and the grouping has not been unblinded. We analyzed the demographic informatics of APOE4 carriers and non-carriers and the changes in cognitive function scores before and after 2 weeks of rTMS treatment. More detailed information was displayed in Supplementary Table 1.

To date, 18 patients with clinically diagnosed Alzheimer’s disease have been included and have received rTMS treatment for 2 weeks. Among them, ten were APOE4 carriers; eight were non-carriers, and there were no significant differences in age, education or gender (Table 2). They were randomly assigned to the high-frequency treatment group or the low-frequency treatment group. Because the study was not blinded, we could not know which subgroup they were assigned to. We could only analyze the overall treatment effect. According to our preliminary results, there was no significant difference in MMSE score, MoCA score except ADAScog (Supplementary Table 1) score between the two groups before and after treatment. When comparing the improvement rate of the two groups, there was a significant difference in the improvement of MoCA score between the two groups. For non- carriers, the MoCA score but not the MMSE or ADAScog score improved by 2.65 ± 3.15, while for carriers, it improved by 0.1 ± 1.7 (*t* = 2.164, *p* = 0.046, Figures 2A–C).

**TABLE 2 T2:** Characteristics of the study cohort.

	APOE4 carriers (*n* = 10)	Non-APOE4 carriers (*n* = 8)	*p*-value
Sex F/M	6/4	5/3	0.914
Age, years	70.37.45	73.756.27	0.312
Education level, years	7.72.98	6.135.37	0.44
MMSE score before rTMS	12.66.77	15.888.54	0.377
MoCA score before rTMS	7.94.28	9.255.50	0.566
ADAScog score before rTMS	39.1316.49	34.8719.03	0.618
MMSE score after rTMS	13.56.22	16.638.73	0.388
MoCA score after rTMS	84.47	11.887.72	0.202
ADAScog score after rTMS	37.1616.39	31.5721.21	0.536

*n, number; F, female; M, male; MMSE, Mini Mental State Examination; rTMS, repetitive transcranial magnetic stimulation; MoCA, Montreal Cognitive Assessment Scale; ADAScog, Assessment Scale-cognitive subscale.*

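### The four-subgroup MMSE rule at P<0.0125 names no contrast or outcome scale; run on MMSE scores it mixes non-randomised genotype differences with the frequency effect and cannot show that rTMS efficacy differs by genotype

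*Protocol article*

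**What the plan says.** All references are to the protocol article.

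- **Objective.** The Objectives section sets out to "analyze the different efficacies of rTMS in AD patients with different APOE genotypes".
- **Hypothesis and outcome.** Under Statistical Hypothesis, "the study hypothesis is to demonstrate the superiority of HF-rTMS over LF-rTMS". Of the primary endpoint it says that "its indicator was the MMSE score".
- **Ordered subgroup steps.** In the same section, "the HF treatment group was preferentially compared with the low-frequency treatment group of non-APOE4 carriers". If that gives P<0.05, "the comparison between the HF treatment group and the low-frequency treatment group of APOE4 carriers is made in order".
- **Last rule.** The section ends with a threshold: if P is below 0.0125, "then the comparison among the four subgroups is considered significant". It gives no null hypothesis, test, list of contrasts or outcome scale, and does not say whether this rule applies only after the two ordered steps.
- **Randomisation.** Stratified Randomized Groups allocates HF or LF within carriers (24 and 24) and within non-carriers (16 and 16).
- **Methods listed.** Statistical Analysis Methods gives the t-test, the Wilcoxon rank sum test and repeated-measures ANOVA. It names no genotype-by-frequency term.

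**The concern.** Three different questions stand side by side: whether HF beats LF, whether the HF-LF difference depends on genotype, and whether four subgroups differ. The third is not a test of either of the first two. Four subgroup means can differ because of frequency, because of genotype, or because of their interaction, and only the interaction bears on the primary objective.

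Randomisation protects HF against LF within a genotype. It gives no protection to carriers against non-carriers, who may differ in MMSE level for reasons unrelated to rTMS.

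At stake is how a result below 0.0125 would be read. The article's Discussion already concludes, from a carrier versus non-carrier difference in 18 patients whose arms are not known, that the genotypes need different treatment schemes. A four-subgroup result declared significant could easily be read the same way.

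**Working it through.** **1. Reproduce the article's figures.**
- Threshold: 0.05/4 = 0.0125. The derivation is not stated, so this fits a Bonferroni level for four comparisons as well as it fits a level chosen for one global test.
- Table 2, MMSE before rTMS ("MMSE score before rTMS 12.66.77 15.888.54 0.377", plus-minus signs lost in extraction): carriers 12.6 (SD 6.77, n = 10), non-carriers 15.88 (SD 8.54, n = 8). Difference 3.28; a pooled t-test gives p = 0.376 (stated 0.377); 95% CI -4.4 to 10.9.
- After rTMS: 13.5 (SD 6.22) and 16.63 (SD 8.73). Difference 3.13; pooled SD about 7.43; p = 0.387 (stated 0.388); 95% CI -4.3 to 10.6.
- Sample Size Calculation: SDs 1.9 and 2.3, difference 2.4, n = 13 and 12. A z calculation with known SDs gives 80.8% power (stated 81%). Root mean square SD = √((1.9² + 2.3²)/2) = 2.11.

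**2. Omnibus reading, on scores.** Assume n = 24/24/16/16, no frequency effect, a genotype gap g and no gating. The noncentrality is λ = (48 × 32/80) × g²/SD² = 19.2 g²/SD², with 3 and 76 degrees of freedom. For g = 3.13 and SD 7.43, λ = 19.2 × 9.80/55.2 = 3.41.

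| Gap g | Rejects at 0.0125, SD 7.43 (Table 2) | SD 2.11 (sample-size section) |
|---|---|---|
| 0 | 1.25% | 1.25% |
| 1 | 2.0% | 18.5% |
| 2 | 5.0% | 83.9% |
| 3.13 | 13.6% | 99.9% |

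With Table 2's unequal SDs (6.22 and 8.73) and scores kept within 0 to 30, simulation gives about 16% at the 3.13-point gap and about 2% at no gap. The unequal SDs therefore add a little on their own; the rest comes from the gap. After about 20% loss (19/19/13/13, SD 7.43) the 13.6% becomes 10.2%.

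**3. Pairwise reading, on scores.** The two HF-LF pairs within genotype stay at 1.25%. One carrier versus non-carrier pair within a frequency (24 v 16, gap 3.13, SD 7.43) rejects in 10.7%. The two such pairs share no patients, so at least one rejects in 1 - (1 - 0.107)² = 20%, against 1 - (1 - 0.0125)² = 2.5% with no gap.

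**4. The contrast that matches the objective.** This is (HF - LF in non-carriers) - (HF - LF in carriers). A constant genotype gap cancels. At 0.0125 with a 3.13-point gap it rejects in about 1.3% of trials with a common SD and about 1.9% with the unequal SDs.

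**5. Change scores.** From Table 2, carriers change by 13.5 - 12.6 = +0.90 and non-carriers by 16.63 - 15.88 = +0.75, a difference of 0.15. The gap almost disappears. But suppose HF beats LF by the planned 2.4 points equally in both genotypes. Then the interaction is zero, and λ = 80 × 1.2²/2.11² = 25.9 at the planning SD. The four-group test rejects in about 97% of trials although nothing is genotype-specific.

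**The case against.** The strongest replies are these.

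- **No null is stated.** A reader might infer that the protocol fixes equality of all four means as its null. It does not. As 0.05/4, the threshold fits a per-comparison level equally well, and on that reading the HF-LF pairs are sound. This stands. However, those two pairs already have their own ordered steps, so a further comparison among four subgroups most naturally adds pairs across genotypes.
- **The gap is not established.** A reader might infer from Table 2 that carriers enter with lower MMSE. The difference is non-significant in 18 patients, with an interval that includes zero and the opposite sign. This stands: the rates above illustrate a possible gap.
- **Repeated-measures ANOVA is listed.** Its group-by-time term would cancel a constant baseline gap, and the article also reports improvement scores. This stands in part. The protocol does not say which term the rule uses, and the between-group main effect would not cancel the gap.
- **The step may be gated.** If it follows the ordered tests, then with no frequency effect it is reached in at most about 5% of trials (one gate) or 0.05 × 0.05 = 0.25% (two). The 13 to 17% could not then occur. This stands as a limit on false rejection, but the text leaves the gating unclear. If frequency does have an effect, the gates open and the difficulty of interpretation remains.
- **Test detail belongs in an analysis plan.** That is true of the model specification. Here, however, the article itself fixes a significance rule and a threshold on a comparison that does not match its objective.

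**Conclusion.** The concern holds in a limited form. The four-subgroup rule is fixed without a contrast or outcome scale. On MMSE scores, either natural reading lets a non-randomised genotype difference contribute to significance. On any scale, a significant four-group result does not show that efficacy depends on genotype.

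The size, about 13 to 17% rejection against 1.25 to 2%, assumes raw scores, no gating, no frequency effect, Table 2's SDs and a true 3.13-point gap. It falls to about 5% for a 2-point gap and rises steeply at the planning SD. On change scores, or behind the ordered tests, the inflation would be small.

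It would go too far to say that the trial's false-positive rate is raised by a known factor: the documents fix neither the null, the scale, the gating nor the gap. The mismatch between the rule and the objective does not depend on those figures.

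**What to change.** In Statistical Hypothesis, before unblinding:

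1. Replace the four-subgroup rule with a test of the genotype-by-frequency interaction on MMSE, adjusted for baseline MMSE, and state its significance level and its place in the testing order.
2. Keep the HF-minus-LF contrasts, overall and within each genotype, as the randomised comparisons.
3. Report the four subgroup means with confidence intervals as description, and make no significance claim about rTMS from carrier versus non-carrier pairs.

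Simply deleting the rule would leave the primary objective without a test, because separate HF-LF tests in each genotype do not compare the two effects.

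The cost is a wording change that uses data already being collected. One nominally confirmatory comparison is lost. The interaction test will have limited power: its standard error is SD × √(2/24 + 2/16) = 0.456 SD, or about 3.4 MMSE points at SD 7.43 and 0.96 at SD 2.11, before any gain from baseline adjustment. The estimate should be reported with its confidence interval, and a non-significant result should not be taken to mean that the genotypes respond alike.
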